#### Patient Self-Report Outcome Measures

##### Primary Outcome Measure

##### Leg Pain

Previous research conducted by the investigators found that pain is one of the most important outcome measures for patients with BRLP[64]. Patients are asked to rate their typical level of leg pain during the past week on an ordinal 11-box scale (0 = no pain, 10 = the worst pain possible)[65]. Several studies have shown that ordinal pain scale measures perform as well as the 10 cm Visual Analog Scale (VAS),[65] a simple, frequently used valid assessment of variation in pain intensity[66,67] and a reliable measure of treatment efficacy[68]. The advantage of the 11-box scale over the VAS is that it is easier to administer and score[66].

##### Secondary Outcome Measures

##### Low Back Pain

Patients with BRLP typically experience low back symptoms[42,49]. Patients are asked to rate their typical level of LBP during the past week on an ordinal 11-box scale as described above.

### Bothersomeness of Symptoms

Using a 0 to 5 scale (0 = not at all bothersome, 5 = extremely bothersome), five items are measured: 1) back pain, 2) buttock pain 3) leg pain, 4) numbness or tingling in leg(s), and/or feet, 5) weakness in leg(s) and/or feet (such as difficulty lifting foot). A BRLP bothersomeness index is calculated by summing the five symptom ratings in a scale (0-25). This index has good internal consistency, construct validity, and responsiveness in BRLP patients[69].

### Frequency of Symptoms

Frequency of the same symptoms described for bothersomeness is measured on a 0 to 5 scale (0 = none of the time, 5 = all of the time). By summing the five symptom ratings, a frequency index is constructed resulting in a 0 to 25 scale. This index has been shown to have good internal consistency, construct validity, and responsiveness[63,69].

### Disability

Disability is measured with the Modified Roland Morris Scale, a 23-item questionnaire that measures the degree to which BRLP restricts patients' daily activities[70,71]. It has a high level of internal consistency, construct validity, and responsiveness, and is scored by simply summing the number of "yes" and "no" answers[69]. A percentage score is calculated based on the number of "yes" scores.

### General Health Status

Functional health status is measured by the reliable, valid, and widely used Medical Outcomes Study Short Form 36-item Health Survey (SF-36v2), which measures eight domains: physical functioning, social functioning, mental health, energy and vitality, pain, general health, and role limitations due to physical and emotional problems[72-74]. This index has been shown to have good internal consistency, construct validity, and responsiveness in sciatica patients[69].

### Fear Avoidance Beliefs

The Fear Avoidance Beliefs Questionnaire (FABQ) was developed to study the relationship between LBP, fear avoidance beliefs and behaviors, and chronic disability[75]. This self-report instrument consists of 16 items, each item answered on a 7 point Likert agreement scale that yields two subscales: work and physical activity. High levels of test-retest reliability have been reported for the work subscale (ICC = .90) and physical activity subscale (ICC = .77)[75,76].

### Patient Satisfaction

Patient satisfaction is measured on 7-point scale (1 = poor, 7 = excellent) using eight questions addressing different aspects of patient care[53].

### Improvement

Patient-rated improvement is an important, patient-oriented outcome measure that has been demonstrated to be reliable and responsive[77-79]. Patients are asked to use the 9-point scale to compare their BRLP condition to what it was before study treatment. Response choices are No symptoms (100% improvement), Much better (75% improvement), Somewhat better (50% improvement), A little better (25% improvement), No change (0% improvement), A little worse (25% worse), Somewhat worse (50% worse), Much worse (75% worse), and Twice as bad (100% worse).

### Medication Use

Non-prescription and prescription medication use are measured using a 5-point scale. Subjects indicate how frequently they have taken medication for their BRLP in the past week. These measures have been used in two previous studies by Bronfort et al[36,53]. To assess the accuracy of medication documentation, patients are asked to bring in their medications at the first baseline evaluation and the week 12 evaluation.

### EuroQol 5D

The EuroQol is a multi-attribute utility scale covering five dimensions (mobility, self-care, usual activities, pain/discomfort, and anxiety/depression) with three levels (no problem, moderate problem, severe problem)[80,81].

### Self-efficacy

Self-efficacy is measured by the Pain Self-Efficacy Questionnaire, a 10-item scale used to assess the level of self-confidence in performing functional and social activities despite the presence of pain. Each item is rated from 0 (Not at all confident) to 6 (Completely confident) and scores range between 0 (no self-efficacy) and 60 (highest self-efficacy)[63,82].

#### Biomechanical and Clinical Objective Measures

A set of six different tests are performed in a single session at BEV2 and repeated at week 12. All objective testing is performed by examiners trained and certified in testing protocols and blinded to patients' treatment assignment. The tests consist of the following:

### Continuous Lumbar Motion

Lumbar motion is assessed using an electromagnetic tracking system (Polhemus Liberty, Colchester, Vermont) and motion monitor software (Innovative Sports Training Inc, Chicago, Illinois), which yields accurate measurement[83]. We have found the angular measurements to be accurate within one degree in our laboratories when compared with a mechanical angular protractor device. Electromagnetic sensors are attached at the thorax and the sacrum using hard plastic plates held in place over bony landmarks with straps. The system acquires three-dimensional position and orientation from the electromagnetic sensors and the relative motion is computed between the trunk and the sacrum using Euler angles. Data are collected using a modified protocol described by Vogt et al[84] for flexion-extension, rotation, side-bending, and circumduction at a sampling rate of 120 points per second. Data reduction is performed using MathCAD software (Mathsoft Inc., Waltham, MA, USA) at PCCR to obtain the following parameters: (1) maximum ranges of motion in the sagittal, coronal, and axial planes and (2) average velocities in the sagittal, coronal, and axial planes from neutral to end ranges.

### Standing Postural Sway

Postural sway data are collected using a method and protocol developed by Bhattacharya et al[85] and adapted for use at PCCR. Patients are blindfolded and stand on a force plate (Model # 4060-NC, Bertec, Inc, Columbus OH) for 30 seconds with a safety harness secured to their torso and attached loosely to the ceiling. Three forces and three moments are collected from the force plate at a rate of 1000 points per second using Motion Monitor software (Innovative Sports Training, Inc, Chicago, IL), which also calculates the x (fore-aft) and y (side-to-side) coordinates of the participant's center of pressure (COP) location, based on dividing the flexion-extension moment by the vertical force and dividing the lateral-bend moment by the vertical force, respectively. The test is repeated with a 10 cm thick section of latex foam placed on top of the force plate. This cycle of measurements is repeated twice, providing four, 30-second COP recordings.

The PCCR Biomechanics Team performs data reduction for patients tested at both sites. For each 30-second segment of data collection, 30,000 points of x-y coordinate data are reduced into 4 COP variables: (1) maximum radial distance the COP traveled from the average location, (2) mean radial distance from the average, (3) total area covered by the COP as it moved during those 30 seconds, and (4) total distance the COP traversed in mm during the 30 seconds. Hence, this assessment produces 8 values--4 from each of 2 different 30-second segments of data collection. With 2 measurement cycles of these data, a total of 16 values are determined from each participant. Reduced data are transferred to the DCC for analysis.

### Neuromuscular Response to a Sudden Unexpected Load

Data are collected using methods and protocols developed by Wilder et al[86] and adapted for use at PCCR that measure muscle activity and COP changes associated with the immediate response to a sudden unexpected force pulling from the participant's chest. EMG electrodes are attached over the paraspinal muscles of the participant bilaterally at the L3 level and connected to an EMG amplifier (Delsys, Inc. Scottsdale AZ). While standing on a forceplate (Model # 4060-NC Forceplate, Bertec, Inc, Columbus OH), participants are fitted with a harness strap around their back at the midsternal level. A load cell (Omegadyne LC101-100, Omegadyne, Inc., Sunbury OH) and accelerometer (Triaxial CXL10LP3, Crossbow Technology, Inc. San Jose, CA) are rigidly attached to the harness. A cord attaches the load cell via a pulley to a 1.8 kg weight that hangs in a PVC tube. The pulley and tube are rigidly attached to a firm concrete wall. The height of the pulley is adjusted so that the cord is horizontal. The participant is blindfolded and wears earphones with loud radio carrier noise to prevent cueing. The weight is raised in the tube between 25 and 35 cm and suspended by a second rope held by the operator's hand. At a signal from the computer operator, the weight is dropped to introduce a sudden tug to the patient's upper trunk.

The Motion Monitor software is triggered by the load cell to record a 4-second segment of data from the two EMG channels, the load cell, accelerometer, and force plate at a rate of 1000 samples/sec. A trial drop is performed with the patient's eyes and ears uncovered to ensure they can tolerate the impact and that an adequate EMG signal is recorded. The force of the tug to the chest depends on the height from which the weight is dropped. The drop distance is adjusted for each patient based on their weight and to ensure that a clear activation of the back muscles can be seen on EMG. Six repetitions of the drop are performed with the blindfold and earphones masking any cues to provide an "unexpected" sudden load.

Raw data collected from both sites is reduced at PCCR using custom software written by Lee[87].

Sixteen variables are collected from each drop including 6 variables that describe the imposed load and subsequent participant movement and 5 paired (left and right sided) paraspinal EMG response factors. The 6 loading and movement factors include: 1) peak force exerted on the participant's trunk, 2) time to that peak force 3) the peak acceleration of the participant's trunk, 4) the time to that peak acceleration, 5) excursion of the participant's COP in the fore-aft direction, and 6) the time to that maximum COP excursion. The EMG factors are: 1) amplitude before the sudden load, 2) length of time from the tug on the harness to the beginning of the EMG responses, 3) magnitude of the maximum EMG responses, 4) time to maximum EMG responses, and 5) duration of the EMG responses.

### Lumbar Paraspinal Muscle Flexion-Relaxation

Our methodology, based on the work of Watson et al,[88] combines the EMG electrode setup of the sudden load test above and the electromagnetic tracking of the continuous lumbar motion to measure the spinal motion and activity of the lumbar paraspinal muscles during a forward bending task. Participants are instructed to move from an upright standing posture into full forward flexion in a smooth manner over 6 seconds. Full flexion is maintained for 1 second followed by a return to the upright position over another 6 seconds. After a 3-second rest, the movement is repeated. A total of three cycles of EMG and position are recorded.

EMG and position data are processed using MathCAD software and custom routines. The EMG signal is rectified and the RMS calculated with a 100 ms window to produce continuous traces of left and right activity with respect to time. The position channels are reduced to provide the lumbar flexion angle. Semi-automated routines locate the maximum EMG activity during the forward flexion task and the minimum activity during the period when the trunk is fully flexed. The flexion/relaxation ratio is calculated as the minimum flexed EMG divided by the maximum during flexion. Previous research has shown that the lumbar paraspinal muscles normally become electrically silent at full forward flexion, whereas patients with low back pain often fail to show this silent period. The flexion/relaxation ratio is a factor that will be used to show the extent to which patients with BRLP exhibit the silent period and whether this factor changes with treatment.

### Torso Muscle Endurance

Blinded examiners measure muscle endurance of the trunk flexors, lateral flexors, and extensors. Tests are performed following a protocol described by McGill[89]. These tests have been shown to be valid and reliable measures of torso muscle endurance[90,91]. Test data consist of the time that each posture is held (in seconds), which are used to calculate ratios. The measurements provide an objective measure of treatment outcome and a baseline guide to the individualized home exercise program.

The EMG sensors are left in place for the extension task of the endurance test. This provides a measure of EMG activity with a known load (trunk weight) to enable calibration of the EMG signal to help with interpretation of the sudden load test; it also provides a measure of EMG activity during fatigue.

### Straight Leg Raise Test

To assess the presence of nerve root irritation, the straight leg raise test is performed by blinded examiners using a digital inclinometer to record angle of leg elevation producing leg symptoms. The straight leg raise test has acceptable reliability[92] and some evidence of validity[93]. With the patient in the supine position, the inclinometer is placed just proximal to the patella and zeroed with the leg in the neutral position. The lower leg is then extended passively until the knee is in full extension; then the whole leg is raised off the table until the patient indicates pain[92]. Test data consists of angle of leg elevation at pain onset and the site of pain.

#### Other Measures

##### Patient Expectation of Care

Prior to treatment group assignment, patients are asked to rate how helpful they think each treatment group will be for their BRLP using an 11-box scale (0 = not at all helpful, 10 = extremely helpful)[94]. Prior to treatment, patients are asked to rate their expectation of improvement using the improvement scale described above.

##### Side-effects

Patients are asked to report side-effects in the patient self-report questionnaires by responding to a list of side-effects generated from previous studies by the investigators assessing SMT and self-care education[42,49]. For each side-effect listed, the patient is asked to indicate if they experienced it, and if yes, to rate the bothersomeness of the side-effect on an 11-box scale (0 = not at all bothersome, 10 = extremely bothersome). This method of recording side-effects is an attempt to standardize side-effect reporting in clinical trials, which has been inadequately addressed in much of the research performed to date[31].

##### Potential Confounding Variables

Health care utilization (dates and types of services for BRLP, type and dose of rescue medications), compliance with the study interventions, and patient expectations is documented in the patient self report questionnaires and the patient file. Clinical depression may also be a confounding variable and is assessed by the Community Epidemiologic Scale-Depression (CES-D), designed for non-psychiatric patients[95]. This one page questionnaire, consisting of 20 depression related questions, was developed by the National Institutes of Health and has been found to be reliable and valid[96].

##### Patient Interviews

Face-to-face interviews are conducted on an individual basis, after the 12 week treatment phase. A schedule of questions is used to direct the interviews and keep the interviewers on a path consistent with the purpose of the study[97]. The questions begin broadly, asking how patients felt about the treatment they received, whether it met their expectations, and what they liked and disliked. These questions are then followed by probe questions to elicit underlying reasons. The format of the interviews is semi-structured with open-ended questions. Permission is sought to tape record the interviews, and participants are assured confidentiality, allowing them to speak freely in response to the questions[98]. All interviews are transcribed for analyses.

To ensure consistency with interview techniques, staff from both sites are trained using standardized protocols[97]. Random samples of 10% of interviews from each site are compared to recorded interviews for accuracy.

##### Data Management

The Data Coordinating Center at PCCR's Office of Data Management and Biostatistics handle all study data. The DCC database system uses password-protected web-based transfer protocols to collect patient management information across sites.

### Statistical Methods

The DCC biostatisticians will conduct data analyses using SAS^® ^(Release 9.0) and S-Plus 7.0 for Windows. Descriptive statistics of patient characteristics will be presented for each treatment group to assess their comparability as well as the generalizability of the sample.

### Data Analysis

Effects in patient-rated leg pain between groups will be assessed by modeling over weeks 3, 12, 26, and 52 adjusting for the baseline value of leg pain and the baseline variables used in the minimization algorithm for treatment allocation. Mixed models, using SAS Proc Mixed, will be used to examine patterns and estimate effects between groups after fitting models that account for the correlation across measurements in the same patient and using the variance-covariance structure that best fits the data[99,100]. Normality assumptions will be evaluated through normal probability plots and transformations explored if necessary. We will test for site-by-group and time-by-group interactions. A level of significance of 0.05 will be used to judge the results as statistically significant. Adjusted mean differences and 95% confidence intervals between groups at weeks 3, 12, 26, and 52 will be presented in tables and line graphs. Further adjustment will control for unbalanced baseline and other possible confounding variables to increase precision of the estimates. An intention-to-treat analysis will be used; all patients with at least one follow-up measure will be included in the analysis, as the methods do not require data at every time point.

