### Randomization

An adaptive computer-generated randomization scheme is used to minimize group differences in 7 baseline factors over all patients enrolled at both sites[52]. The scheme attempts to provide the best balance of the following baseline characteristics: age (< 50 years vs. ≥ 50 years); duration of leg pain at the BEV2 (< 12 weeks, 12-25 weeks, 26-51 weeks, 1-5 years, and > 5 years); presence or absence of neurological signs in the leg (QTF classification 2 or 3 vs. classifications 4 or 6); distress at the BEV2 (SF-36 items positive vs. negative for distress); positive straight leg raise test at BEV2 (≤45 degrees vs. ≥45 degrees); amount of time spent driving a vehicle (< 2 hours several times per week vs. 2 or more hours several times per week); and leg pain aggravation with coughing or sneezing (no vs. yes). All study personnel are blinded to upcoming treatment assignments and the biomechanics objective examiners are blinded to treatment assignment throughout the course of the trial. The algorithm was programmed by the DCC Database Programmer and the database is maintained by the DCC Data Manager. The back-up treatment assignment protocol is by predetermined sequentially numbered, opaque envelopes prepared by the DCC Data Manager and maintained by the Project Manager at each site.

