### Sample Size

Sample size projections were based on a power analysis using SAS Proc GLMPower. In the latest pilot study by WHCCS, group differences in pain of 8 percentage points after 3 months of treatment were observed[42]. Informed by these results, the scientific literature,[31,101] and consensus of study investigators and clinicians, we are interested in detecting an 8 percentage point difference between the two group means in patient-rated leg pain at the short- and long-term. In our pilot study, correlation coefficients among the pain variable over time varied from r = 0.22-0.25 and estimates of standard deviation were 1.7 (scale 0-10).

Using these estimates, the sample size calculation based on the analysis of covariance at one time point, adjusting for the baseline value, indicates 80 patients per group are required to achieve 86% power at the 0.05 level of significance to detect a difference between groups of 8 percentage points.

The same data analysis approach will be used to analyze the secondary outcome variables as confirmatory analyses to assist with the interpretation of study results. A more conservative Bonferroni-adjusted level of significance will be used to judge the results as statistically significant.

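### As most naturally read, the leg-pain model adjusts for age and straight leg raise in their two-level allocation forms; continuous terms would gain a little precision from data already held

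*Protocol article*

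**What the plan says.** The Data Analysis section sets the covariates of the leg-pain mixed model, which covers the four follow-up assessments and is described as "adjusting for the baseline value of leg pain and the baseline variables used in the minimization algorithm for treatment allocation". The same section allows further adjustment for unbalanced baseline and other confounding variables. The Sample Size section carries the same approach over to the secondary outcomes.

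The Randomization section lists seven minimization factors. Two of them are cuts of quantities measured on a continuous scale: "age (< 50 years vs. ≥ 50 years" and "positive straight leg raise test at BEV2 (≤45 degrees vs. ≥45 degrees". Duration of leg pain is also grouped, but into five levels.

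The Straight Leg Raise Test section describes blinded examiners "using a digital inclinometer to record angle of leg elevation producing leg symptoms", and the objective tests are done at BEV2. How age is recorded is not described, but age in years is implied by the age criteria.

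**The concern.** The Data Analysis sentence points to the variables that the algorithm uses, and the only definitions given for age and straight leg raise are two-level. An analyst who follows the text would enter two binary terms.

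Cutting is sensible for allocation. In the analysis model it treats a patient of 51 like one of 80, and a leg raise of 50 degrees like one of 85. If age or angle predicts follow-up pain, part of that prediction stays in the residual variance and chance imbalance within each category is left unadjusted. The confidence intervals for the adjusted mean differences are then wider than the collected data require, for leg pain and for every secondary outcome analysed the same way. No bias or type I error problem is at stake.

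**Working it through.** **Inputs from the Sample Size section.** Target: "detecting an 8 percentage point difference between the two group means in patient-rated leg pain", which is 0.8 on the 0-10 scale. Variability: "correlation coefficients among the pain variable over time varied from r = 0.22-0.25 and estimates of standard deviation were 1.7 (scale 0-10". Stated result: "80 patients per group are required to achieve 86% power at the 0.05 level of significance". The test is taken as two-sided.

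**Step 1: reproduce the stated power.** Residual SD = 1.7 × √(1 − r²). Noncentrality = 0.8 / (SD × √(2/80)). Power comes from the noncentral t with baseline pain as the only covariate.

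- r = 0.22: SD 1.658, noncentrality 3.05, power 85.8%.
- r = 0.25: SD 1.646, noncentrality 3.07, power 86.3%.

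The stated 86% is reproduced with no credit for age or straight leg raise.

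**Step 2: information kept by a cut.** For a normal covariate with a linear effect, cut so that a share p lies below, the share of explained variance kept is φ(z_p)² / [p(1 − p)].

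- p = 0.5: 0.637
- p = 0.4: 0.622
- p = 0.2: 0.490

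**Step 3: power with cuts against continuous terms.** The document gives neither the correlations with follow-up pain nor the splits. Assumed: 40% of patients below the age cut, 20% below the leg-raise cut, the same correlation ρ for each covariate, and covariates independent of each other and of baseline pain. With r = 0.25, 80 per group and 11 covariate degrees of freedom (baseline pain 1, duration 4, six two-level factors 6):

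- R² with cuts = 0.0625 + ρ² × (0.622 + 0.490)
- R² continuous = 0.0625 + 2ρ²
- Residual SD = 1.7 × √(1 − R²)

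| ρ (assumed) | R² cuts | R² continuous | Power, cuts | Power, continuous | Gain (points) | Variance ratio |
|---|---|---|---|---|---|---|
| 0 | 0.063 | 0.063 | 86.3% | 86.3% | 0 | 1.00 |
| 0.1 | 0.074 | 0.083 | 86.7% | 87.0% | 0.3 | 1.01 |
| 0.2 | 0.107 | 0.143 | 87.9% | 89.1% | 1.2 | 1.04 |
| 0.3 | 0.163 | 0.243 | 89.8% | 92.5% | 2.7 | 1.11 |

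Confidence-interval width scales with the square root of the variance ratio. The cuts make intervals about 0.5% wider at ρ = 0.1, 2% at 0.2 and 5% at 0.3.

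Other splits give similar answers. With both covariates split 50/50 or both 20/80, and ρ taken as a partial correlation given baseline pain, the gain is 0.2-0.3 points at 0.1, 1.0-1.3 at 0.2 and 2.0-2.9 at 0.3. With 96 per group (192/2) and no loss to follow-up, it is at most 2.0 points.

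**Step 4: cost in degrees of freedom.** At ρ = 0.2, power is 89.12% with 11 covariate degrees of freedom, 89.12% with 13 (two continuous terms beside the coded factors) and 89.11% with 14 (a missing-angle indicator as well). The cost is negligible.

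**Step 5: cost of losing patients.** At ρ = 0.2 the variance ratio is 1.04, so dropping about 4% of patients (1 − 1/1.04) would cancel the gain. A missing angle therefore has to be handled.

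**The case against.** The strongest reply is that the coding is not stated. The Data Analysis section names the variables and not their form, and a statistical analysis plan that is not shown may settle it. That stands as far as it goes: the cut form is the natural reading, not an explicit commitment. But the sentence refers to variables that the article defines only as categories, so it steers the analyst to the cuts.

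A reader might infer that power built into the sample size is being lost. The document does not support this. The 86% rests on baseline pain alone and holds under either coding, and every scenario with cuts in the table is at or above it. Only a possible bonus is forgone.

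The size is also open to challenge, and fairly. All of it rests on assumed correlations, and zero is possible. At ρ = 0.3, age and leg raise would each predict follow-up pain better than baseline pain does, at the protocol's own 0.22-0.25, so that row is optimistic.

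Adjusting for the factors as used in allocation is a legitimate analysis; that stands. The provision for further adjustment could bring in continuous age or angle, but it does not commit to either.

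Finally, replacing the cut by the angle could drop patients who have none, since a mixed model omits records with a missing covariate. Keeping the coded factor beside the angle does not rescue them. This is right, and the fix must deal with it.

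**Conclusion.** The point holds as a modest improvement, not as an error. On the natural reading, the model uses two-level age and straight leg raise where continuous values exist. The analysis is valid and the planned power is intact. The forgone precision is about 0 to 1.2 power points for assumed correlations of 0 to 0.2, and about 2.7 at 0.3. These figures rest on normal, linear, mutually independent covariates, the assumed 40% and 20% splits, and 80 patients per group.

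Duration of leg pain is grouped too, but five levels keep more of the information than a two-level cut, so it is a lesser case.

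**What to change.** In the Data Analysis section, or the analysis plan if it governs the coding:

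- Keep all minimization factors as coded.
- Add age in years as a continuous covariate, with its form (linear, or a low-order spline) fixed in advance.
- Add the BEV2 straight leg raise angle as a continuous covariate. For patients with no angle at pain onset, use a fixed fill-in value plus an indicator, based on baseline data only, so that nobody with a follow-up measure leaves the model.
- Use the same covariate set for the secondary outcomes.

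The coded leg-raise factor also needs its boundary stated, because exactly 45 degrees falls in both levels as printed.

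The cost is one degree of freedom for linear age, one for a linear angle and one for the indicator if it is needed; a spline would add a few more. The functional form and the missing-angle rule must be fixed before unblinding. No new data and no extra patient burden are involved. Age alone carries no missing-angle problem and could be added by itself if the angle proves awkward.

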### Rescue Medication and Surgical Consultation

Prescription strength rescue medication is available for patients experiencing severe pain and is prescribed as needed by a medical doctor. A clinical decision-making rule agreed upon by the medical clinicians is used to manage acute exacerbations. Patients may receive NSAIDs, opioids, and/or muscle relaxants. Any patient who demonstrates progressive neurological signs or severe, intractable pain is removed from study treatment and referred for surgical consultation. These patients continue to be followed and remain in the intention-to-treat analysis.

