### Analysis of Biomechanical Measures

First, baseline measures of continuous spinal motion, postural sway, response to sudden load, and flexion-relaxation in the patients with BRLP will be compared to data (unpublished) from previous trials of patients with sub-acute and chronic low back pain *without *radicular pain. Next, we will explore effects of these measures after 12 weeks of active care, taking into account gender and body mass index. If there are unbalanced baseline or other confounding variables, we will also control for these in the analysis. Finally, we will examine and describe the bivariable relationships between our primary outcome, leg pain, and each biomechanical variable.

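### Further adjustment for possible confounders is not limited to pre-randomisation variables, and the only list of them includes care use, rescue medication and compliance

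*Protocol article*

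**What the plan says.** Under Data Analysis, the group effect on leg pain comes from a mixed model over weeks 3, 12, 26 and 52, adjusted for baseline leg pain and the variables used in the minimisation. After describing how the adjusted differences will be presented, the section adds: "Further adjustment will control for unbalanced baseline and other possible confounding variables to increase precision of the estimates". An intention-to-treat analysis is promised directly afterwards.

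The article has a section headed "Potential Confounding Variables". It names "Health care utilization (dates and types of services for BRLP, type and dose of rescue medications), compliance with the study interventions, and patient expectations", and then depression measured by the CES-D.

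The biomechanical outcomes get a similar rule: "If there are unbalanced baseline or other confounding variables, we will also control for these in the analysis". The Sample Size section carries the leg-pain analysis approach over to the secondary outcomes.

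**The concern.** The adjustment sentence names two groups of variables: baseline variables that look unbalanced, and other possible confounders. The second group is set apart from baseline and nothing restricts it to measures taken before allocation. The one list that could fill it contains three items that are, or can be, consequences of treatment.

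In a randomised comparison such variables are not confounders. Conditioning on them removes any part of the effect that runs through them. It can also create a spurious arm difference through underlying severity, even where the variable has no effect of its own on pain. The further-adjusted difference would then not estimate the intention-to-treat effect. The stated aim of precision is a reason to use prognostic baseline covariates, and gives no support for variables that treatment can change.

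A smaller, separate weakness is that choosing baseline covariates because they look unbalanced fixes the model after the arms have been compared. That does not condition on consequences of treatment, but a pre-specified list avoids it.

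**Working it through.** **1. The plan's own figure.** Inputs from Sample Size: difference 8 percentage points = 0.8 on the 0-10 scale, SD 1.7, r = 0.22-0.25, 80 per group, level 0.05 (taken as two-sided). Residual SD = 1.7 × √(1 − r²) = 1.658 (r = 0.22) or 1.646 (r = 0.25). Power = Φ(0.8 / [SD × √(2/80)] − 1.96) = 86.2% or 86.7%; with the noncentral t, 85.8% or 86.3%. The stated 86% is reproduced. It belongs to a model adjusted for the baseline value only.

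**2. Which listed items are safe covariates?**

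| Item | Timing | Safe in a treatment-effect model? |
|---|---|---|
| Patient expectations | "Prior to treatment group assignment, patients are asked to rate how helpful they think each treatment group will be" (Patient Expectation of Care) | Yes |
| CES-D | Not stated where it is listed | Yes, if taken at baseline |
| Compliance with study interventions | Exists only after allocation | No |
| Rescue medication | "Prescription strength rescue medication is available for patients experiencing severe pain and is prescribed as needed by a medical doctor" (Rescue Medication and Surgical Consultation) | Not when given on study; its trigger is close to the primary outcome |
| Health care use for the condition | Follow-up use can respond to pain and to arm | Not when it arises on study |

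The arms also differ in contact: up to 20 manipulation visits in one arm, on top of the four education sessions that both receive. An arm difference in compliance or care-seeking is therefore plausible.

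**3. Size of the shift.** In a linear model, shift = (arm difference in the covariate) × (within-arm slope of pain on the covariate). The article gives neither term. Assume that rescue use is 10-20 percentage points lower in the arm with less pain, and that users report 0.7-1.5 points more pain:

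- smallest: 0.10 × 0.7 = 0.07, which is 0.07/0.8 = 9% of the target difference;
- largest: 0.20 × 1.5 = 0.30, which is 0.30/0.8 = 38%.

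Under these assumptions the shift is toward zero. If the arm difference or the slope has the opposite sign, it goes the other way.

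**4. Range under a simple causal model (all inputs assumed).** Let the covariate have within-arm SD 1 and be shifted by *a* through treatment. Unmeasured severity raises the covariate by *u* and pain by 1.3*u*, and the covariate has its own effect *b* on pain. With the total effect held at −0.80, the adjusted difference is −0.80 − *a*(*b* + 1.3*u*²).

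| *a* | *u* | *b* | Adjusted difference |
|---|---|---|---|
| 0 | any | any | −0.80 |
| −0.2 | 0.6 | 0 | −0.80 + 0.2 × 0.468 = −0.71 |
| −0.4 | 0.6 | 0 | −0.80 + 0.4 × 0.468 = −0.61 |
| −0.6 | 0.6 | +0.3 | −0.80 + 0.6 × 0.768 = −0.34 |
| −0.6 | 0.3 | −0.3 | −0.80 − 0.6 × 0.183 = −0.91 |

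A simulation with 400,000 patients per setting agrees. The outcome SD in these settings was 1.22-1.52, below the article's 1.7, so the figures show the mechanism and are not a forecast.

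**5. What such a shift would mean for power.** If 10%, 25%, 40% or 50% of a true 0.8 were removed, 0.72, 0.60, 0.48 or 0.40 would remain. Power at 80 per group would be 79%, 64%, 45% or 34%, with the residual SD held at 1.646. A covariate related to pain would reduce that SD, so these values may overstate the loss.

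**The case against.** The strongest reply is that the article nowhere says that it will adjust for rescue medication, care use or compliance. The adjustment sentence does not refer to the list, the list carries no analysis instruction, and the aim of precision suits baseline covariates. A baseline-only reading is therefore open, and the full covariate list may stand in an analysis plan that is not shown.

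Much of this stands. The link rests on near-identical terms and on there being only one list. That list does not label its items as post-randomisation; the timing follows from what they are. Some care use or rescue medication might also be recorded before allocation, since Baseline Evaluation One mentions rescue medication too, and such baseline records would be acceptable covariates. Expectations are measured before assignment.

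What does not stand is the appeal to missing detail. The rule is written down, separates other confounders from baseline variables, and excludes nothing. An analyst who followed it with the article's own list would condition on consequences of treatment.

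A reader might also infer that the trial's main result is biased, or that the plan has two competing primary estimates. The documents do not support that. The model described first uses baseline covariates only, and the natural reading is a main model with a supplementary one. The main conclusion is affected only if the further-adjusted estimate is reported as the treatment effect, which the text leaves open.

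**Conclusion.** The point holds as a badly fixed rule. As written, further adjustment may include health care use, rescue medication and compliance, and doing so would bias the further-adjusted difference relative to the intention-to-treat effect in the same section. The bias requires that the assigned arm affects these variables; if it does not, the illustration shows none.

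The size and direction cannot be derived from the article. The shift of 0.07-0.30 points (9-38% of the 0.8-point target) and the range of 0.34 to 0.91 rest entirely on assumed inputs. The baseline-adjusted model and its 86% power are unaffected, and no change in sample size follows. The remaining gap is that the text does not name that model as primary.

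**What to change.** 1. In Data Analysis, state that the model adjusted for baseline leg pain and the minimisation factors is the primary one.
2. In Data Analysis and in Analysis of Biomechanical Measures, limit any further adjustment to a pre-specified list of pre-randomisation variables, in place of variables picked for observed imbalance. Candidates are site, the baseline value of the outcome analysed, expectation before allocation, and CES-D if taken at baseline. Keep gender and body mass index for the biomechanical measures, as already planned.
3. Report health care use, rescue medication and compliance by arm descriptively, or in sensitivity or mediation analyses labelled as such, and revise the section that lists them as potential confounders to match.

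The cost is wording only: no new data and no new patients. The sponsor gives up a little freedom to adjust after seeing the data.
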